#### 1.2.2 Secondary objectives

##### 1.2.2.1 Clinical outcomes

We will assess the acute and long-term effects of the treatment on several clinical features of MDD: remission (MADRS_10_ < 10) and response (reduction of at least 50% in MADRS_10_ score), severity of self-rated depression (BDI_13_), physical and social anhedonia and apathy immediately after the treatment, after 1-month and 3-month follow-up.

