#### 2.4.2 Other clinical and behavioral outcomes

Several clinical and behavioral features will be assessed using:

- the 10-item MADRS total scores to assess depression severity.- the number of responders, defined as those who show a reduction of at least 50% in their MADRS score.- the 13-item Beck Depression Inventory (BDI) (Gould, 1982), to assess self-rated depression.- the 11-item Young Mania Rating Scale (YMRS) (Young et al., 1978), to assess manic states.- the Childhood Trauma Questionnaire (CTQ) (Bernstein et al., 2003) to study early life adversity.- the Chapman Social Anhedonia Scale and the Chapman Physical Anhedonia Scale (Chapman et al., 1976) to investigate respectively physical and social anhedonia.- the Snaith-Hamilton Pleasure Scale (SHAPS) (Snaith et al., 1995) to assess global anhedonia.- the Apathy Evaluation Scale (AES) (Marin et al., 1991) to assess apathy.- the Free-Viewing task (FVT) to assess cognitive biases, more precisely, early and sustained emotional attentional biases.

These outcomes will be assessed before and after the 50 iTBS sessions. The same outcomes will also be assessed at 1 and 3 months after treatment and compared between the two groups. In addition, the relationship between early life adversity and depression severity will be examined, as well as its association with the evolution of depressive symptoms and especially anhedonia.

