##### 4.2.1.2 Early life adversity

Childhood trauma and maltreatment negatively affect rTMS-left DLPFC treatment outcome in patients with MDD (Hu et al., 2021). Therefore, the short form of the CTQ will be used, which includes 28 items, rated from 0 to 5 according to the occurrence of the event experienced. It allows to identify 5 different types of trauma: emotional neglect, physical neglect, emotional abuse, physical abuse, and sexual abuse. Subtotals can be calculated for each type of trauma to provide a nuanced understanding of the participant's childhood trauma experiences.

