##### 4.4.1.2 Clinical data analysis

The proportion of remissions and responses will be investigated using chi-squared tests or Fisher's exact test. Changes in scores of depression severity, anhedonia and olfactory capabilities over the study period within the two groups will be analyzed using a mixed 2-way repeated measures ANOVA (GROUP^*^TIME) or a generalized linear mixed model depending on the distribution of the data. Pearson correlations will be performed to examine the relationship between olfactory anhedonia and pre-treatment physical and social anhedonia, as well as the relationship between childhood trauma severity and response to treatment, the relationship between childhood trauma severity and anhedonia (physical, social, and olfactory), and the relationship between childhood trauma severity and depression severity. Type of medication and type of depression (unipolar vs. bipolar) will be included in the analysis. We did not expect differences in response between patients with unipolar and bipolar depression.

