##### 4.4.1.3 Behavioral data analysis

Changes in early and sustained attention within the two groups will be investigated using a mixed 2-way repeated measures ANOVA (GROUP^*^TIME) or a generalized linear mixed model, depending on the distribution of the data. Pearson correlations will be performed to examine the relationship between changes in depression severity and changes in emotional attentional biases.

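### Childhood trauma is to be correlated with response, which the protocol defines only as a yes/no MADRS cut, although the stated objective is the graded course of symptoms

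*Protocol article*

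**What the plan says.** Section 1.2.2.1 (Clinical outcomes) introduces "response (reduction of at least 50% in MADRS_10_ score" as a secondary outcome. Section 2.4.2 lists "the number of responders, defined as those who show a reduction of at least 50% in their MADRS score". Both are the same yes/no cut.

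Section 4.4.1.2 (Clinical data analysis) opens in that sense: "The proportion of remissions and responses will be investigated using chi-squared tests or Fisher's exact test". Later in the same paragraph it names a method for associations, "Pearson correlations will be performed to examine the relationship between olfactory anhedonia and pre-treatment physical and social anhedonia", and continues the list with "as well as the relationship between childhood trauma severity and response to treatment". Trauma severity is then also to be correlated with anhedonia and with depression severity.

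Section 2.4.2 words the trauma objective differently. It covers the link between early life adversity and depression severity, "as well as its association with the evolution of depressive symptoms and especially anhedonia".

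Section 4.2.1.2 gives the reason for using the Childhood Trauma Questionnaire (CTQ): "Childhood trauma and maltreatment negatively affect rTMS-left DLPFC treatment outcome in patients with MDD".

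**The concern.** Someone following section 4.4.1.2 literally would take the one defined meaning of response and correlate a graded CTQ score with a 0/1 indicator cut from the 0–60 MADRS. That differs from what section 2.4.2 says is of interest, and it ignores how far each patient moved on either side of the 50% line.

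Two things are at stake. The first is sensitivity: an association that the protocol itself gives as the reason for collecting the CTQ would be harder to detect. The second is interpretation. A Pearson coefficient with a 0/1 variable cannot reach 1 in the usual way and depends on the response rate, so it is not on the same footing as the graded trauma correlations listed beside it. Leaving the variable open also leaves a choice between a binary and a graded outcome to be made after the data are seen.

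**Working it through.** **Which variable is meant.** For the binary reading:
- both definitions of response are the 50% cut;
- section 4.4.1.2 itself treats responses as proportions;
- where a graded change is meant, the text says so, as in section 4.4.1.3: "relationship between changes in depression severity and changes in emotional attentional biases".

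For the graded reading:
- section 2.4.2 states the trauma objective as an association with how symptoms evolve;
- the other trauma correlations in the list use graded scores.

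The text does not settle it.

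**Inputs.** The protocol gives no expected correlation, response rate or power for this analysis, so there is no figure of its own to reproduce. From the document: 74 evaluable patients and 80 recruited (section 2.6.1), and alpha 0.05 (section 4.4.1). Assumed: two-sided testing, CTQ and MADRS change bivariate normal, response rate p between 30% and 70%, and a range of true correlations r.

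**Shrinkage.** Cutting a normal variable so that a proportion p respond multiplies the correlation by φ(z_p) / √(p(1−p)).
- p = 0.30 or 0.70: 0.759, a reduction of 24.1%.
- p = 0.40 or 0.60: 0.789, a reduction of 21.1%.
- p = 0.50: 0.798, a reduction of 20.2%.
- p = 0.20 or 0.80, outside the assumed range: 0.700, a reduction of 30.0%.

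A true r of 0.30 would therefore appear as 0.30 × 0.759 = 0.228 to 0.30 × 0.798 = 0.239.

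**Power.** By Fisher's z, c = atanh(r) × √(N − 3) and power = Φ(c − 1.96) + Φ(−c − 1.96). For the binary outcome, r is first multiplied by the factor above. Example with N = 74 and r = 0.30: c = 0.3095 × √71 = 2.61, power 74%. With p = 0.30, r becomes 0.228, c = 1.95 and power is 50%.

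| True r (N = 74) | Graded | 0/1, 50% respond | 0/1, 30% or 70% respond | Points lost |
|---|---|---|---|---|
| 0.1 | 13.5% | 10.3% | 9.8% | 3–4 |
| 0.2 | 40.1% | 27.3% | 25.2% | 13–15 |
| 0.3 | 74.2% | 53.9% | 49.7% | 20–25 |
| 0.4 | 94.6% | 79.6% | 75.2% | 15–19 |
| 0.5 | 99.6% | 94.5% | 92.0% | 5–8 |
| 0.6 | 100.0% | 99.3% | 98.5% | under 2 |

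With N = 80 the losses are 14–16, 20–25 and 13–18 points at r = 0.2, 0.3 and 0.4. Over both sample sizes the range for r of 0.2–0.4 is therefore about 13–25 points. Simulation with 20,000 datasets per setting agrees within about 1–2 points. For example, at N = 74, r = 0.30 and 30% responders it gave 74.0% against 49.7%, with mean coefficients of 0.296 and 0.225.

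**The case against.** The strongest reply is that the binary reading is not established. The word response is also used loosely: section 4.4.1.2 speaks of no expected difference in response between unipolar and bipolar patients, and the Discussion speaks of varied clinical response. The trauma items in section 4.4.1.2 line up well with the objective in section 2.4.2 if response is taken there as symptom change. Pearson correlation would then be an ordinary choice and nothing is lost. This stands, and it makes the point one of reconciliation rather than of a settled error.

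Second, a Pearson correlation with a 0/1 variable is a valid test, equivalent to comparing mean CTQ between responders and non-responders with a t-test. This also stands. A reader might infer that the planned analysis is invalid, or that it is biased for its own target. The document does not support that, since the analysis would correctly estimate association with response as defined.

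Third, section 4.4.1 provides a non-parametric fallback, and section 4.4.1.2 says that medication type and depression type will enter the analysis. The fallback changes the test but not the dichotomised variable. The covariates argue for a regression, because a simple Pearson coefficient cannot carry them.

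Fourth, such detail often belongs in an analysis plan, which is not shown. The point here is not that detail is absent: the protocol names a method and a defined term, and that term does not match its own objective.

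**Conclusion.** Section 4.4.1.2 and section 2.4.2 describe the trauma question with different outcomes. If the defined meaning of response is used, the analysis is valid but less informative. The coefficient is about 20–24% smaller than with the graded outcome, and power is about 13–25 points lower for a true r of 0.2–0.4.

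These figures rest on a roughly normal MADRS change, 30–70% responders and about 74–80 patients. The document gives neither the distribution nor the response rate, and it gives no expected correlation. It would be tempting to state the loss as a fact about this trial, but that is not supported. It is smaller for weaker or stronger correlations, would be smaller if MADRS change were strongly bimodal, and is nil if a graded change was intended.

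The analysis is secondary and was not used to size the trial. The primary comparison of remission is untouched. This is a worthwhile clarification, not a serious flaw.

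**What to change.** In section 4.4.1.2, replace the correlation of trauma severity with response by a linear regression of the post-treatment (week-2) MADRS total on CTQ severity. Adjust it for baseline MADRS, randomised arm, and the medication type and depression type that the section already says will be included, and report the partial correlation for CTQ. This matches the objective in section 2.4.2 and removes the ambiguity on either reading. Adjusting for arm is sensible because the protocol expects the arms to differ widely (30% against 60% remission, section 2.6.1).

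Keep the 50% response for comparing proportions between arms. If a responder version of the trauma question is also wanted, use logistic regression and label it supportive.

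The cost is a sentence or two of analysis wording. Table 1 already schedules the CTQ at week 0 and MADRS at weeks 0 and 2, so no patients, visits or procedures are added.

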##### 4.4.1.3 Behavioral data analysis

Changes in early and sustained attention within the two groups will be investigated using a mixed 2-way repeated measures ANOVA (GROUP^*^TIME) or a generalized linear mixed model, depending on the distribution of the data. Pearson correlations will be performed to examine the relationship between changes in depression severity and changes in emotional attentional biases.

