#### 1.1.4 Aim and hypotheses

This study aims to electrochemically stimulate the DA reward circuitry to alleviate anhedonia and achieve remission in patients with treatment-resistant MDD. We therefore propose to increase DA release from ventral tegmental area neurons and thereby increase ventral striatal activity, which is reduced in anhedonia. For this purpose, we will combine rTMS applied over the left DLPFC with hedonic olfactory stimulation (i.e., odorants with pleasant hedonic value), both known to modulate the DA reward system.

- By stimulating the DLPFC with rTMS, we aim to enhance its feedback control over subcortical structures.- By using odorants with positive hedonic value known to recruit/activate the reward circuit, we aim to enhance DA release and thereby increase ventral striatal activity which is reduced in anhedonia,

Based on evidence linking anhedonia to reduced DA transmission and blunted mesocorticolimbic network functional connectivity (Phillips et al., 2023), we hypothesize that rTMS would alleviate depressive symptoms through changes in functional and effective connectivity within DA-related brain regions.

We propose that the combined approach may be more effective in enhancing DA release, as both methods stimulate DA activity, resulting in greater improvements in anhedonia and a more pronounced reduction in depressive symptoms compared to rTMS alone.

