#### 2.4.3 Neurobiological outcomes

The brain connectivity and activity within the brain regions involved in the reward and olfactory circuitry we will be explored through functional Magnetic Resonance Imaging (fMRI) and dual-site transcranial magnetic stimulation protocol. This will be assessed before and after the treatment, and compared between the two groups. The relationship between changes in neurobiological outcomes and changes in clinical features will be also investigated.

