## 3 Methods: assignment of intervention

### 3.1 Sequence generation

Patients will be randomly assigned (1:1) to receive either iTBS alone or iTBS combined with pleasant olfactory stimulation. Computer-generated random numbers using the Sealed Envelope platform (https://www.sealedenvelope.com) will be used to generate the allocation sequence. Block of 2, 4, and 6 will be used to stratified the randomization.

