##### 4.4.1.4 Neurobiological data analysis

The fMRI data will be preprocessed and analyzed according to the most recent standard procedures in the field available at the time of analysis. For the dual-site TMS protocol, a ratio of the MEP amplitude evoked by the dual-site TMS to the MEP amplitude evoked by single TMS over M1 will be performed. This ratio will be analyzed using a mixed 2-way repeated measures ANOVA (GROUP^*^TIME) or a generalized linear mixed model depending on the distribution of the data. Pearson correlations or multiple linear regressions will be performed between neurobiological and clinical and behavioral data.

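### The planned correlations between post-randomisation changes make no provision for randomised arm, so an odorant effect on both variables could appear as a patient-level link

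*Protocol article*

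**What the plan says.** Patients are allocated in equal numbers: "Patients will be randomly assigned (1:1) to receive either iTBS alone or iTBS combined with pleasant olfactory stimulation" (section 3.1). Two parts of the analysis plan then relate outcomes measured after randomisation to each other.

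- **Attentional bias (section 4.4.1.3).** "Pearson correlations will be performed to examine the relationship between changes in depression severity and changes in emotional attentional biases". Pearson correlation is the only method named. The preceding sentence, on change over time, includes a group-by-time term; the correlation sentence does not mention group.
- **Brain measures (section 4.4.1.4).** "Pearson correlations or multiple linear regressions will be performed between neurobiological and clinical and behavioral data". No rule for choosing between the two is given and no covariates are listed. Section 2.4.3 confirms that changes are to be related to changes: "The relationship between changes in neurobiological outcomes and changes in clinical features will be also investigated".

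The only covariates named in the analysis sections are in the clinical section, 4.4.1.2: "Type of medication and type of depression (unipolar vs. bipolar) will be included in the analysis". Arm is not among them. Section 1.1.4 supplies the interpretation that the brain analyses are meant to inform: "we hypothesize that rTMS would alleviate depressive symptoms through changes in functional and effective connectivity within DA-related brain regions".

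**The concern.** A Pearson correlation is bivariate and has no place for arm. Computed over all randomised patients, it combines the association between patients within an arm with the difference between the two arm means. If the combined treatment moves both variables, the arm means separate on both axes. The pooled correlation is then non-zero even when, within each arm, patients who change more on one variable do not change more on the other.

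The trial's own hypothesis makes such separation plausible: section 1.1.4 expects the combination to reduce symptoms more than rTMS alone. A marker could also separate the arms without any role in mood. Section 4.2.3.2 measures effective connectivity while patients smell odorants, and under section 2.3 only one arm is exposed to pleasant odorants during 50 sessions. That exposure alone might shift the measure. An unadjusted correlation cannot tell this from a patient-level link between brain change and symptom change.

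At stake is the reading of the secondary, mechanistic results.

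**Working it through.** **Plan's own figures.** The protocol gives no design figure for the correlations. I take N = 80 (40 per arm) and the remission rates of 30% and 60% from section 2.6.1, and the threshold of 0.05 from section 4.4.1, read as two-sided (an assumption). The inflation reproduces: 74/(1 − 0.07) = 79.6, so 80. The 37 per group does not: the two-sided arcsine formula gives 42. That is a separate matter and does not enter below.

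**Step 1: symptom difference between arms.** On a latent normal scale, d1 = z(0.60) − z(0.30) = 0.253 + 0.524 = 0.78 SD. A logistic scale gives (ln 1.5 − ln 0.4286) × √3/π = 0.69 SD.

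**Step 2: marker difference between arms.** The documents give none for attentional bias or any brain measure. I vary d2 from 0 to 0.78 SD.

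**Step 3: induced correlation.** With equal arms, within-arm SD of 1 and within-arm correlation of 0,

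r = (d1·d2/4) / √[(1 + d1²/4)(1 + d2²/4)].

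For d1 = d2 = 0.78: 0.1521/1.1521 = 0.13. For d1 = 0.78 and d2 = 0.5: 0.0975/√(1.1521 × 1.0625) = 0.09. If either d is 0, r is 0.

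**Step 4: rejection rates.** Simulation with 40,000 replicates, no within-arm association, nominal 5%:

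| d1 | d2 | Induced r | Unadjusted, N = 80 | Unadjusted, N = 74 | Arm-adjusted, N = 80 |
|---|---|---|---|---|---|
| 0.78 | 0 | 0.00 | 5.0% | 4.9% | 5.0% |
| 0.78 | 0.3 | 0.05 | 7.7% | 7.4% | 5.0% |
| 0.78 | 0.5 | 0.09 | 12.0% | 11.8% | 4.8% |
| 0.78 | 0.78 | 0.13 | 21.6% | 20.5% | 5.2% |
| 0.5 | 0.5 | 0.06 | 8.4% | 7.7% | 5.1% |
| 0.3 | 0.3 | 0.02 | 5.4% | 5.4% | 5.0% |

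With 0.7 SD on both, close to the logistic conversion, r = 0.1225/1.1225 = 0.11, and a separate simulation of 20,000 trials at N = 80 gave 16.6%.

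**Step 5: what the shared treatment does.** Both arms receive active iTBS. A benefit common to both shifts the two arm means equally, leaves d1 and d2 unchanged, and so adds nothing to r. Only the effect added by the odorant counts.

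**The case against.** The best defence is that the protocol is silent rather than wrong. It does not say that the arms are pooled, and covariates for secondary correlations are often left to an analysis plan, which is not shown here. For brain data, section 4.4.1.4 allows multiple regression, which could include arm. These points stand as limits on the claim: pooling is an inference, and the regression route is open. They do not remove it. Section 4.4.1.3 names one method, and that method cannot carry arm as a covariate. Section 4.4.1.4 leaves the same method open. Section 7.3 also presents the article as the full protocol.

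The induced r of at most 0.13 is also below the 0.22 needed for significance at N = 80. That is true of the average, but sampling variation still carries up to 22% of trials past the threshold.

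Four stronger readings are tempting, and the documents do not support them:

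- **Any effective treatment creates the artefact.** It does not. The shared iTBS benefit induces no correlation, and the odorant must move both variables.
- **The error rate is 22%.** That figure needs a marker effect as large as the symptom effect, and the documents give no marker effect.
- **The childhood-trauma correlations in section 4.4.1.2 are affected in the same way.** The exposure in "the relationship between childhood trauma severity and response to treatment" predates randomisation, so arm cannot systematically shift it.
- **The protocol will treat these correlations as proof of mediation.** It does not say so. Section 1.2.2.3 speaks of exploring and investigating relationships, and section 4.2.2.1 presents the attention task as a correlate of severity.

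**Conclusion.** The point holds for correlations between post-randomisation changes: the only method in section 4.4.1.3 and the Pearson option in section 4.4.1.4. Followed as written over all patients, they are confounded by arm whenever the odorant affects both variables. With a symptom difference of 0.78 SD and a marker difference of 0 to 0.78 SD, the artefactual r is 0 to 0.13. The false-positive rate, judged against no within-arm association, is 5% to 22% at N = 80.

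The range rests on three assumptions: that the remission contrast, a threshold on the end-of-treatment score, converts to a similar standardised difference in change scores; that the marker effect lies in the range shown; and that the test is two-sided. This is a secondary-analysis issue. It does not touch the remission comparison or the stopping rule.

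**What to change.** In section 4.4.1.3, replace the Pearson correlation with a partial correlation, or a regression, that has randomised arm as a covariate; a pooled within-arm correlation would serve equally. In section 4.4.1.4, state the same for analyses of change against change, and drop the unadjusted Pearson option for them. One sentence covers both sections. Arm adjustment alone returns the rate to 5%, so no further covariates or interaction terms are needed for this purpose.

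The cost is one degree of freedom per analysis. Allocation is already recorded, so no new data are required. The wording should be settled before the allocation is revealed to the analyst; a coded arm variable lets the analyst stay blinded, as section 4.4.1 requires.

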##### 4.4.1.4 Neurobiological data analysis

The fMRI data will be preprocessed and analyzed according to the most recent standard procedures in the field available at the time of analysis. For the dual-site TMS protocol, a ratio of the MEP amplitude evoked by the dual-site TMS to the MEP amplitude evoked by single TMS over M1 will be performed. This ratio will be analyzed using a mixed 2-way repeated measures ANOVA (GROUP^*^TIME) or a generalized linear mixed model depending on the distribution of the data. Pearson correlations or multiple linear regressions will be performed between neurobiological and clinical and behavioral data.

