#### 4.2.2 Behavioral assessment

##### 4.2.2.1 Eye tracking free-viewing task

The Free Viewing Task (FVT) will assess attentional emotional bias before the treatment and after 1, 5, and 50 rTMS sessions, as it correlates with depression severity (Imbert et al., 2024). This makes it a relevant outcome to evaluate before and after treatment, providing objective measures of improvement. In the task, pairs of faces: one emotional (happy or sad) and one neutral, are presented randomly for 3,500 ms to the right and left of a fixation cross. The inter-stimulus interval is randomized among 1,250, 1,500, or 1,750 ms, and the next pair appears only when the participant fixates on the cross. A total of 32 pairs (16 happy- neutral, 16 sad-neutral pairs), with 16 different identities (8 males, 8 females), will be presented. The faces are extracted from the FACES database (Ebner et al., 2010).

Throughout the task, gaze position and eye movements are recorded using an eye-tracking system (SMI SensoMotoric Instruments with BeGaze 3.6.52, Teltow, Germany).

We will assess early and sustained attention allocation using eye-movement recordings. Sustained attention will be measured by dwell time (DT), the total time spent fixating on faces. The emotional bias score will be the difference between DTs for emotional and neutral faces. Early attention will be measured by the orientation of the first saccade, the first face the participant looks at. The laterality quotient will be the difference between the number of first saccades to emotional vs. neutral faces, divided by the total trials. Positive values indicate a bias toward emotional faces; negative values indicate a bias toward neutral faces.

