##### 4.2.3.2 Effective connectivity with Dual-site transcranial magnetic stimulation

The MagStim 200^2^ BiStim^2^ dual-site TMS (MagStim, United Kingdom), connected to two 40 mm figure-of-eight coils, will be used to probe effective connectivity from the left DLPFC to the left M1 both at rest and during odor perception (pleasant and unpleasant odorants) sent using an olfactometer (Wang et al., 2020; Neige et al., 2023). When the olfactometer (Sezille et al., 2013) detects the exhalation phase, it initiates an airflow through tubes containing the odorant for 6 seconds. This odorant-charged airflow is delivered to the participant via nasal canula. At 600 ms following the onset of the inhalation phase, which represents the maximum conscious representation of the odorant (Kato et al., 2022), the olfactometer trigs the TMS to deliver a pulse to the DLPFC. After a brief delay, a trigger is sent to the TMS connected to M1 to administer a pulse.

This measure will be realized before and after the 50 sessions of iTBS. Motor-evoked potentials (MEP) will be recorded using surface electromyography (BIOPAC, United States of America) from the right FDI. The conditioned MEP peak-to-peak amplitude evoked by dual-site TMS will be compared to the MEP amplitude evoked by TMS applied over M1 alone (see Neige et al., 2023) for the detailed protocol of this experiment.

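### The dual-site TMS ratio has one visit before and one after treatment, so its group-by-time test is a change-score test that leaves the baseline unused as a covariate

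*Protocol article*

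**What the plan says.** Section 4.4.1.4 of the protocol article forms the ratio of the motor evoked potential under dual-site stimulation to that under stimulation of M1 alone. It then says "This ratio will be analyzed using a mixed 2-way repeated measures ANOVA"; the model in full is a "mixed 2-way repeated measures ANOVA (GROUP^*^TIME) or a generalized linear mixed model depending on the distribution of the data". No baseline covariate is named.

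The timing is consistent throughout. Section 4.2.3.2 says "This measure will be realized before and after the 50 sessions of iTBS". Section 2.4.3 says of the neurobiological outcomes "This will be assessed before and after the treatment, and compared between the two groups". Table 1 marks dual-site TMS for patients at weeks 0 and 2 only. At each visit the measure is taken at rest and during pleasant and unpleasant odorants (section 4.2.3.2), so each patient has one before-and-after pair per condition.

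Allocation is randomised 1:1 (section 3.1).

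**The concern.** With only two time points, a group-by-time interaction asks whether the mean change differs between arms. The change score subtracts the whole baseline value, including its measurement noise. A model of the post-treatment value with the baseline as covariate subtracts only the fraction that the data support. Under randomisation both target the same arm difference, and the adjusted version is never less precise in large samples.

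The ratio is the trial's measure of effective connectivity, and section 1.1.4 expects rTMS to work through changes in functional and effective connectivity. The sample size in section 2.6.1 was set for remission, and no power is stated for this ratio. The choice of model is therefore a lever on sensitivity that costs nothing. With the planned test, a real effect of the odorants on DLPFC–M1 connectivity is more likely to be missed in the same patients.

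**Working it through.** **Inputs from the protocol.** Two arms, 1:1 (3.1); one visit before and one after treatment (2.4.3, 4.2.3.2, Table 1); group-by-time test (4.4.1.4); alpha 0.05 (4.4.1), taken here as two-sided. Section 4.4.2 limits analysis to patients with a pre-treatment and at least one post-treatment evaluation and fills gaps by LOCF, so the analysed data are pairs.

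**Inputs not in the protocol, hence assumed.** The pre-post correlation r, and k, the pre-treatment SD divided by the post-treatment SD.

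**Plan's own figure.** None exists for this analysis. The only sample-size figure, 37 per group, concerns remission. Sample size cancels from the ratio of variances below, so that figure does not enter.

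**Step 1: the identity.** On one simulated two-visit data set with 37 per arm, the t statistic was 2.732 for the two-sample test of change and 2.732 for the group-by-time term. A Gaussian mixed model with group-by-time gave the same estimate (0.532) and statistic.

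**Step 2: the variances.** With post-treatment SD s, the per-patient variances are:

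- change score: s²(1 + k² − 2kr)
- baseline-adjusted: s²(1 − r²)

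The difference is s²(k − r)². The share of precision (inverse variance) lost is therefore (k − r)² / [(k − r)² + 1 − r²]. At k = 1 this reduces to (1 − r)² / [2(1 − r)] = (1 − r)/2.

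**Step 3: equal SDs (k = 1, s = 1).** The standard-error column is 1 − √[(1 + r)/2]. Extra patients is 2/(1 + r) − 1. The last column is Φ(2.802·√[(1 + r)/2] − 1.960), the power of the change-score test where the adjusted test has 80%.

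| r | Var. change, 2(1 − r) | Var. adjusted, 1 − r² | Precision lost | SE reduction from adjusting | Extra patients for change score | Power of change score |
|---|---|---|---|---|---|---|
| 0 | 2.00 | 1.00 | 50% | 29% | 100% | 51% |
| 0.3 | 1.40 | 0.91 | 35% | 19% | 54% | 62% |
| 0.5 | 1.00 | 0.75 | 25% | 13% | 33% | 68% |
| 0.7 | 0.60 | 0.51 | 15% | 8% | 18% | 73% |
| 0.9 | 0.20 | 0.19 | 5% | 2.5% | 5% | 78% |

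In 8,000 simulated trials per value of r with 37 per arm, the loss was 34%, 24% and 12% at r = 0.3, 0.5 and 0.7. This is slightly below the formula, as expected when the slope has to be estimated.

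**Step 4: unequal SDs.** The loss vanishes when k = r, for example k = 0.5 with r = 0.5. At k = 0.8 it is 22%, 11% and 2% for r = 0.3, 0.5 and 0.7. At k = 1.25 it is 50%, 43% and 37%. Over k from 0.5 to 1.25 and r from 0.3 to 0.7, the range is 0% to 50%.

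**The case against.** The strongest reply is that nothing here is wrong. A change-score test is valid and unbiased in a 1:1 randomised comparison, it is conventional, and the outcome is a secondary one that sections 1.2.2.3 and 2.4.3 describe as exploratory. This stands, and it sets the weight of the point. It does not make the choice a good one, because the protocol names the model and a better one uses data already collected.

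A second reply is that the mixed-model alternative might escape the problem. In part it does: the exact equivalence holds for a Gaussian, identity-link model and not for another family or link. But the protocol switches to that model on distribution, not to adjust for baseline. An SAP may settle the covariates; the point concerns only the model that the protocol states.

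A reader might also extend the point to other outcomes, which the documents do not support:

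- **Free-viewing task.** Section 4.4.1.3 has it "investigated using a mixed 2-way repeated measures ANOVA", and Table 1 shows two visits. But section 4.2.2.1 places it "before the treatment and after 1, 5, and 50 rTMS sessions", section 1.2.2.2 agrees, and section 2.4.2 adds follow-up. With four or more visits the interaction is no longer a change-score test and the formula above does not apply.
- **fMRI.** Section 4.4.1.4 leaves it to standard procedures at the time of analysis, so there is no group-by-time model to replace.
- **Clinical scales.** Section 2.4.2 says "The same outcomes will also be assessed at 1 and 3 months after treatment and compared between the two groups", so these are not before-and-after pairs. The apathy scale has two visits in Table 1 but more in the text.

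**Conclusion.** The point holds for the dual-site TMS ratio alone, as an avoidable loss of efficiency and not as an error. The identity with a change-score test is exact within each condition for the ANOVA and for a Gaussian mixed model with group-by-time.

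The size is conditional. It would be tempting to say that the plan gives up 15% to 35% of its precision, but that range needs r between 0.3 and 0.7 and equal SDs at both visits, and the protocol states neither. With equal SDs the loss runs from 50% at r = 0 to 5% at r = 0.9; with unequal SDs it can be close to nil. These are losses in inverse variance. On the scale on which a confidence interval is read, r from 0.3 to 0.7 means a standard error about 19% to 8% smaller with adjustment.

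Nor does the point reach the main result. Section 4.4.1.2 states "The proportion of remissions and responses will be investigated using chi-squared tests or Fisher's exact test", so remission is not tested by group-by-time.

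**What to change.** In section 4.4.1.4, for the dual-site TMS ratio in each condition, replace the group-by-time test with a linear model of the week-2 value on arm and the week-0 value of the same condition. If the ratio is skewed, put both visits on the same transformed scale. Report the adjusted arm difference with its 95% CI.

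Leave the fMRI wording as it is. Apply the same model to the free-viewing scores only if the conflict between Table 1 (two visits) and sections 1.2.2.2 and 4.2.2.1 (four visits) is resolved to two.

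The cost is a few words in one section and one degree of freedom in the model, with no new data and no added patients. Section 5.1.2 repeats the secondary analyses at the interim look at 40 patients, so the change is best recorded before that look.
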